
### Randomization

2.4

Patients who meet all the inclusion criteria and none of the exclusion criteria and consent to take part in the trial after they have received the study oral and written information, will then be randomly assigned in equal proportions to either THC, CBD, THC + CBD, or placebo using stratified block randomization. Randomization will be stratified by sex and baseline mean spasticity score. In each of the 4 strata, corresponding to different combinations of sex (male vs. female) and baseline mean spasticity score ([2-6[vs. ≥6), randomization will be performed using blocks of size 4. This will minimize the imbalance between group sizes, while preventing unblinding of the treatment allocation of consecutive participants. The randomization schedule will be generated by CHUM’s Centre for the Integration and Analysis of Medical Data (CITADEL), who will send the randomization codes to the CHUM research pharmacy and keep secure digitalized copies. Randomization codes will be maintained throughout the study.

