#### Secondary and exploratory outcomes

2.6.3

All the secondary – efficacy and safety – outcomes will be assessed at baseline, at week 4 and 12 weeks after the initial treatment period. Clinical efficacy outcomes are presented in Table 2. In addition, we will assess the success of participants’ blinding after the initial treatment period with the James Blinding Index (69). Blood tests will be conducted only at baseline and at week 4 to measure immunological and neurobiological markers. Safety measures will include all reported or observed adverse events and serious adverse events (AEs and SAEs). Pregnancy and birth control will be re-evaluated every 4 weeks.

**Table 2 tab2:** Secondary and exploratory efficacy assessments.

Test	Symptom	Type of outcome
Modified Ashworth Scale (42)	Spasticity, as assessed by a clinician	ClinRO
Expanded Disability Status Scale (43)	Disability	
Positive and Negative Syndrome Scale (45)	Psychotic symptoms	
Multiple Sclerosis Quality of Life Inventory (46, 47), including^a^:		PRO
MOS Pain Effects Scale (46, 47)	Pain	
Modified Fatigue Impact Scale – 5-Item Version (46, 47)	Fatigue	
Bowel Control Scale (46, 47)	Bowel dysfunction	
Bladder Control Scale (46, 47)	Bladder dysfunction	
Modified Social Support Survey – 5-Item Version (46, 47)	Perceived social support	
Sexual Satisfaction Scale (46–48)	Sexual dysfunction	
36-Item Short Form Survey (46, 47)	Quality of life	
Perceived Deficits Questionnaire (46, 47, 49)	Subjective cognitive function	
Pittsburgh Sleep Quality Index (50) and Epworth Sleepiness Scale (51)	Sleep issues, according to the assessment of sleep quality and sleepiness, respectively	
Restless Legs Syndrome Severity Rating Scale (52, 53)	Restless legs syndrome’s severity	
Hospital Anxiety and Depression Scale (54, 55)	Anxiety and depression	
Cannabis Experience Questionnaire (56, 57)^b^	Euphoric and paranoid-dysphoric effects of cannabis	
Battery of cognitive tests: Montreal Cognitive Assessment (58), Brief Visuospatial Memory Test–Revised (59), D-KEFS Color-Word Interference Test (60), Hopkins Verbal Learning Test–Revised (61), The Trial Making Test A/B (62), and Symbol Digit Modalities Test (63)	Objective cognitive function	PerfO
Timed 25 Foot-Walk test (64–66)	Mobility	

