### Data analyses

2.7

The data will be analyzed once all randomized subjects have completed the trial. Analyses of primary and secondary outcomes will rely on the intention-to-treat paradigm. Thus, all initially randomized subjects will be included. Descriptive statistics will be used to compare the baseline characteristics of subjects. They will include means, medians, standard deviations and interquartile ranges for continuous variables, and frequencies and percentages for categorical variables. Sensitivity analysis will be performed to the first few participants who did not complete the NRS scale as per the last version of the protocol and consequently have a different primary outcome measure.

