#### Primary endpoints

2.7.2

Firstly, an analysis of variance (ANOVA) will be used to assess the treatments effect on the differences in the mNRS from baseline to week 4. The normality of the responses will be assessed using normal-quantile plots. The ANOVA model will only include the factors THC and CBD. Secondly, an analysis of covariance (ANCOVA) will be used to evaluate the treatments effect on the post-intervention mNRS while adjusting for baseline mNRS and sex (stratification variables). The ANCOVA may reduce potential bias present in the ANOVA model (74). Finally, the ANCOVA model described above will be expanded by including potential confounders, such as biomarkers, for which a clinically meaningful difference between any two groups will be revealed by the preliminary descriptive analysis. The estimated adjusted and unadjusted differences in mNRS from baseline to week 4 and their 95% confidence intervals will be reported for all models.

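### The third primary-endpoint model picks its covariates by chance imbalance between arms rather than by prognostic value, so it is not fixed until the data are seen

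*Protocol article*

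**What the plan says.** Section 2.7.2 of the Protocol article sets out three analyses of the primary endpoint, in order.

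1. An ANOVA of the change in mNRS from baseline to week 4: "The ANOVA model will only include the factors THC and CBD".
2. An ANCOVA of the post-intervention mNRS, adjusted for baseline mNRS and sex.
3. An extension of that ANCOVA: "the ANCOVA model described above will be expanded by including potential confounders, such as biomarkers", the ones chosen being those "for which a clinically meaningful difference between any two groups will be revealed by the preliminary descriptive analysis".

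Estimates and 95% confidence intervals are to be reported for all three. None is named as primary. Section 2.7.3 applies the same methods to the secondary and exploratory outcomes, so the selection rule carries over to them.

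Three other statements bear on the rule. Section 2.4 has participants "randomly assigned in equal proportions to either THC, CBD, THC + CBD, or placebo". Section 2.7 says "The data will be analyzed once all randomized subjects have completed the trial" and, of the descriptive step, "Descriptive statistics will be used to compare the baseline characteristics of subjects". Section 2.6.3 says "Blood tests will be conducted only at baseline and at week 4 to measure immunological and neurobiological markers".

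**The concern.** With sound randomization, any difference between arms in a baseline covariate is a chance difference. Its size is therefore a poor guide to whether adjustment helps. What matters is how strongly the covariate predicts the outcome, and the rule has no such criterion. A strong predictor that happens to look balanced stays out, and an irrelevant marker that happens to differ goes in.

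Two features widen the net. A difference between any two of four arms gives each covariate six chances to qualify. What counts as clinically meaningful for a biomarker is left to judgement, and that judgement is made when the outcomes already exist.

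At stake are the precision of the adjusted estimate and the standing of a model whose content cannot be known in advance. That model sits beside two fixed ones with no stated rank among the three.

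**Working it through.** **Inputs.** Four arms at 1:1:1:1 (2.4). Target N=250, so 250/4 = 62.5 per arm; the lower target of 200 gives 50 per arm (2.7.1). The article gives no figure of its own for this rule to reproduce. The threshold and the number of candidate covariates are not stated, so both are assumptions here and are shown as ranges.

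**Step 1: how often chance triggers the rule.** For a normally distributed baseline covariate in SD units, each arm mean has standard error 1/√n. Some pair of arms differs by more than t exactly when the range of the four means exceeds t, so

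P(any pair) = P(studentized range, k=4, > t√n).

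For one pair named in advance, P = 2[1 − Φ(t/√(2/n))].

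Example at N=250 and t=0.25: t√n = 0.25 × √62.5 = 1.976, giving 50%. For one named pair, 0.25/√(2/62.5) = 1.398, giving 16%.

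| Threshold (SD) | Any pair, N=250 | One named pair, N=250 | Any pair, N=200 |
|---|---|---|---|
| 0.20 | 68% | 26% | 75% |
| 0.25 | 50% | 16% | 60% |
| 0.30 | 34% | 9% | 44% |
| 0.40 | 11% | 2.5% | 19% |
| 0.50 | 2.7% | 0.5% | 6% |

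With 10 independent candidates (assumed) at N=250, the expected number admitted by chance is 6.8, 5.0, 3.4, 1.1 and 0.3. The chance that at least one is admitted is above 98% at 0.30 SD or less, 70% at 0.40 SD and 24% at 0.50 SD.

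**Step 2: what the rule does to the estimate.** This was simulated with 62 per arm (N=248), no treatment effect, and 10 independent standard-normal candidates of which 2 are prognostic. Outcome = 0.4X₁ + 0.4X₂ + 0.5 × baseline + noise with SD 0.65, with 6,000 runs per threshold. All fits include THC, CBD and baseline. These strengths are assumptions, not trial figures.

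Analytic anchors for the standard error of the THC effect:

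- With X₁ and X₂ in the model: 2 × 0.65/√248 = 0.083.
- With neither: 2 × √(0.65² + 2 × 0.4²)/√248 = 2 × 0.862/15.75 = 0.109.

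| Threshold (SD) | Empirical SD: rule / prespecified | Mean reported SE: rule / prespecified | Type I error, rule | Non-prognostic covariates admitted | At least one prognostic covariate omitted |
|---|---|---|---|---|---|
| 0.2 | 0.087 / 0.083 | 0.093 / 0.083 | 3.8% | 5.5 | 54% |
| 0.3 | 0.094 / 0.082 | 0.102 / 0.083 | 3.5% | 2.7 | 89% |
| 0.5 | 0.108 / 0.083 | 0.109 / 0.083 | 4.9% | 0.2 | about 100% |

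The reported standard error, and so the confidence interval, is wider than under prespecified adjustment by 0.0933/0.0829 = 1.13, 0.1021/0.0830 = 1.23 and 0.1090/0.0830 = 1.31. A loose threshold admits noise; a strict one discards useful predictors. At 0.2 and 0.3 SD the reported standard error exceeds the empirical SD, which is why the tests are slightly conservative.

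**The case against.** Most of the case on the other side concerns stronger readings, and on those it is right.

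- **Invalid p-values.** A reader might infer that data-driven selection inflates type I error. It does not here: the trigger compares arms on covariates and never looks at the outcome, and the simulated error was 3.5% to 4.9%.
- **Adjustment for week-4 biomarkers.** Since markers are drawn at baseline and week 4, a reader might infer that post-treatment values could enter and absorb part of the effect. Section 2.7 ties the descriptive comparison to baseline characteristics, so baseline values are very probably meant. Section 2.7.2 does not repeat the restriction, which calls for a clarification and no more.
- **A steered primary result.** The expanded model is the last of three, the first two are fixed, and all are to be reported. It cannot silently replace the ANCOVA on baseline mNRS and sex.
- **Many covariates admitted by chance.** This depends on the threshold. It holds at 0.20 to 0.30 SD and fails at 0.50 SD.

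It can also be said that a candidate list and a cut-off belong in an analysis plan that is not shown. That is fair, and their absence is not the point. Nor is the rule worse than adding nothing: in the simulation its empirical SD was no larger than that of the ANCOVA on baseline alone (0.108 to 0.110).

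What remains is the principle that the article does state, namely selection by observed difference between arms. A list or cut-off elsewhere would narrow the discretion but would not supply the missing prognostic criterion.

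**Conclusion.** The point holds as a weakness of a stated rule in one of three models for the primary endpoint. Selection by chance imbalance leaves that model undefined until the data are seen. It also gives a less precise estimate than prespecified prognostic covariates at each threshold simulated, with confidence intervals about 13% to 31% wider under the assumed prognostic strengths. The chance that a single covariate qualifies at N=250 runs from 68% at 0.20 SD to 2.7% at 0.50 SD.

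These sizes rest on an assumed threshold, independent normal candidates, and an assumed 2 prognostic covariates in 10. The direction of the precision loss does not depend on the exact values, provided that the prespecified covariates really are prognostic.

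Type I error is not threatened. The change is worth making because it is cheap, because no model is named primary, and because the same methods extend to the secondary and exploratory outcomes.

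**What to change.** In section 2.7.2:

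1. Delete the selection of covariates by observed difference between arms.
2. In its place, fix before unblinding a short list of baseline covariates chosen for expected prognostic value from data already collected. Age and Expanded Disability Status Scale score, added to baseline mNRS and sex, are examples; the trial team should confirm their prognostic value.
3. Label this model supportive.
4. State that only baseline values may enter efficacy models, and that week-4 biomarkers are analysed separately as mechanistic outcomes. This agrees with the baseline comparison in section 2.7.

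The cost is wording only: no new data, visits or participants. Observed baseline differences can still be described in the baseline table without driving the model.

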#### Secondary and exploratory endpoints

2.7.3

The secondary and exploratory outcomes will be analyzed using the same methods as spasticity. Exploratory outcomes and mechanistic factors (sex, neurobiological markers, age, etc.) will be analyzed using ANCOVA models.

##### Sex and gender-based analysis

2.7.3.1

Numerous publications have documented the impact of sex on multiple aspects of MS (biology, epidemiology, pregnancy) and substance use, respectively (75–78). Our statistical plan will include stratified analyzes to identify the sex-linked immune mechanisms as well as the sex-specific effects of cannabis.

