### Study population

2.3

The CANSEP study seeks to identify a cohort of PwMS according to the 2017 revised McDonald criteria (23), from the Centre hospitalier de l’Université de Montréal (CHUM) MS Clinic. Our study sample will be representative of the sex distribution of MS, which is 2.6 higher in women than in men in Canada (1). It will recruit adults of at least 21 years of age [the legal age in the province of Quebec to use cannabis products (24)], who reported a mean level of spasticity over 7 days of 2 points or more on the mNRS. All potential participants will be screened to determine their eligibility according to the following inclusion and exclusion criteria:

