#### Sample size and power calculation

2.7.1

The sample size for this trial was calculated using ‘pwr.t.test’ (for a Student t-test) in the ‘pwr’ package in R statistical software (70). The required sample size was estimated to ensure at least 80% power, with a two-sided alpha significance level of 5%, to detect clinically important effects of the two factors THC and CBD, on spasticity, which is the primary outcome (71). A target total recruitment of 200 patients would cover scenarios with a mean change from baseline among treated patients ranging from −1.90 to 1.55, where −1.55 is what we consider to be the minimal clinically significant effect (22, 33, 72, 73). However, some power would be lost upon Bonferroni adjustment. Thus, a target total recruitment of 250 patients would be more adequate, after accounting for a potential rate of attrition of 5% over the study period, based on previous studies (22, 33, 72, 73) and the clinical experience at the CHUM MS Clinic.

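### Sex-specific effects are to be identified by separate analyses in women and men, with no treatment-by-sex interaction or between-sex contrast stated

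*Protocol article*

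**What the plan says.** Section 2.7.3.1 of the protocol article gives the method for the sex question in one sentence: "Our statistical plan will include stratified analyzes to identify the sex-linked immune mechanisms as well as the sex-specific effects of cannabis". Sex is also among the factors in the third aim (section 1.2), which concerns mechanisms of benefit and harm.

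Three other places bear on the point:

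- **Section 2.7.2** puts sex in the primary ANCOVA as an adjustment variable, because it is a stratification factor. It also promises estimated differences with 95% confidence intervals for all models.
- **Section 2.7.3** says that "mechanistic factors (sex, neurobiological markers, age, etc.) will be analyzed using ANCOVA models". It does not list model terms.
- **Section 2.7.6** names the only interaction in the article, THC by CBD.

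On the size of the strata, section 2.3 says the sample will reflect the sex distribution of MS, "which is 2.6 higher in women than in men in Canada". Section 2.7.1 sets the sample size for the overall THC and CBD effects: "The required sample size was estimated to ensure at least 80% power", and after allowing for multiplicity and attrition "a target total recruitment of 250 patients would be more adequate". No power or precision is stated for the sex analyses.

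**The concern.** A sex-specific effect is a statement that the treatment effect in women differs from that in men. Separate analyses yield one effect per sex. Unless the two are contrasted, nothing in the output measures the difference or its uncertainty. A main effect of sex in an ANCOVA does not do so either: it compares the outcome level between the sexes, not the effect of THC or CBD.

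The unequal split adds to the exposure. The male stratum holds little more than a quarter of the sample, so an effect equal in both sexes can easily reach significance in women and miss it in men. Readers tend to take that pattern as evidence that a treatment works in one sex only. The article promises guidance for patients and clinicians (sections 3 and 4), so such a message could travel beyond the paper.

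**Working it through.** **The plan's own figure.** The total of 200 cannot be reproduced, because section 2.7.1 gives neither an SD nor a placebo change. It gives changes among treated patients, "where −1.55 is what we consider to be the minimal clinically significant effect". The standardised effect can only be back-solved. A two-sample t-test at two-sided 5% with 80% power needs d = 0.398 for a factor margin (100 v 100), or d = 0.566 for one arm against another (50 v 50). The first matches the stated aim of detecting the effects of the two factors. It is an assumption here, not a planned value.

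**Inputs**

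- N = 250 (section 2.7.1). Under intention to treat, with missing follow-up of the primary outcome replaced by the baseline value (sections 2.7 and 2.7.5), all 250 enter the primary-outcome analysis.
- Sex ratio 2.6 to 1 (section 2.3).
- Equal allocation within sex, since sex is a randomisation stratum (section 2.4). Half of each sex is therefore at each level of a factor.
- Two-sided 5%. The text says "However, some power would be lost upon Bonferroni adjustment" but not for how many tests.
- Assumed: the same true effect and SD in both sexes.

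**Stratum sizes**

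- Women: 250 × 2.6/3.6 = 180.6, or 90.3 per factor level.
- Men: 250 × 1/3.6 = 69.4, or 34.7 per factor level.

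**Within-sex significance when the effects are equal, d = 0.398**

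- Power in women 0.758; in men 0.373.
- Women only: 0.758 × (1 − 0.373) = 0.475.
- Men only: 0.373 × (1 − 0.758) = 0.090.
- Exactly one sex: 0.475 + 0.090 = 0.565, about 57%.
- Simulation at N = 250 (6,000 runs): women only 47.3%, men only 10.0%.

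**Range over the unknown effect size (N = 250, effect equal in both sexes)**

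| True effect (SD) | Power, women | Power, men | Significant in women only |
|---|---|---|---|
| 0.20 | 27% | 13% | 23% |
| 0.30 | 52% | 23% | 40% |
| 0.398 | 76% | 37% | 47% |
| 0.50 | 92% | 54% | 42% |
| 0.566 | 97% | 64% | 35% |
| 0.70 | 99.7% | 82% | 18% |
| 0.80 | >99.9% | 91% | 9% |

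The peak is just under 48%, near 0.41 SD. With no effect in either sex it is 0.05 × 0.95, about 5%.

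**Sensitivity to other inputs.** With 237.5 analysed (5% attrition), power is 74% in women and 36% in men, and women-only significance is again 47%. At alpha 0.025 (an assumed Bonferroni level for two factors) and 80% overall power, it is also 47%.

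**The direct comparison.** For a factor effect in SD units, the SE of the between-sex difference is √(4/180.6 + 4/69.4) = 0.282. The 95% half-width is 1.96 × 0.282 = 0.55 SD (0.57 SD with 237.5). The SE of the overall factor effect is √(4/250) = 0.126, so the interaction SE is 0.282/0.126 = 2.23 times as large. In the simulation, with equal effects, the interaction test was significant in 5.1% of runs.

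**Power of the interaction test.** For a sex difference as large as 0.398 SD, 0.398/0.282 − 1.96 = −0.55, which gives about 29%. If the overall effect itself has only 80% power at the final N, power for a sex difference of that size is about 24%.

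**The case against.** The strongest reply is that the text does not describe the error. A reader might infer that sex specificity will be judged by which stratum is significant, but section 2.7.3.1 states no such rule. Section 2.7.2 promises estimates with confidence intervals, and section 2.7.3 applies the same methods to the other outcomes. The two strata are independent, so the difference and its interval can be derived from the stratum results. It would therefore be too strong to say that the plan cannot test a sex difference or that the difference will never be estimated.

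The sentence also says what the analysis will include, not that it will stop there. The ANCOVA sentence in section 2.7.3 leaves room for an interaction, and a full analysis plan not shown here may specify one.

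A reader might also take 0.40 SD and 47% as the trial's planning figures. They are not: the effect is back-solved, and 47% is close to the top of the range. It is moreover the chance of a discordant pattern of significance, not of a wrong published conclusion, which would need someone to misread that pattern.

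All of this stands, and it limits the point. It does not remove it. The article names a method for identifying sex-specific effects, and that method, as stated, lacks the comparison that would identify them. The low power of the interaction test does not favour stratification either. The data carry the same limited information both ways, and the interaction estimate shows it openly.

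**Conclusion.** The point holds in limited form. Stratified analyses are named as the way to identify sex-specific effects and sex-linked immune mechanisms, and no between-sex comparison of treatment effects is stated anywhere in the article. If within-sex significance were used to judge sex specificity, equal effects would give significance in women only in about 47% of trials at a true effect of 0.40 SD, and in about 9% to 48% across 0.2 to 0.8 SD. An interaction test would be significant in about 5%.

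These figures rest on 250 analysed, the 2.6 to 1 ratio being achieved, equal SDs in the two sexes, a factor-margin comparison at two-sided 5%, and a back-solved effect size. The method point needs none of them. The matter is worth correcting, but it concerns a secondary or exploratory analysis and leaves the primary ANOVA and ANCOVA conclusions untouched.

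**What to change.** - Add THC × sex and CBD × sex to the ANCOVA, which already contains sex.
- Name the between-sex difference in each factor's effect, with its 95% CI, as the analysis of sex-specific effects.
- Show the effects in women and in men from that same model as description, without separate claims of significance.
- Apply the same rule to the immune markers.
- State in advance that the result is read as an estimate, since the interaction test has low power.

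The cost is a few lines in the analysis plan, best written before the data are analysed. No new data are needed, and sex is already a randomisation stratum. The downside is an interval that will be visibly wide, with a half-width of about 0.55 SD at N = 250, and that will rarely settle whether the sexes differ.
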